### Allocation

Each subject will have four suction blister wounds, two on each thigh. Wounds will be labelled R1 (right thigh, distal), R2 (right thigh, proximal), L1 (left thigh, distal) and L2 (left thigh, proximal).

A computer-generated randomisation list will be created using SAS Proc Plan, SAS V.9.4 by a designated responsible person at Clinical Trial Consultants AB. The randomisation list will contain subject number, wound position, thigh (left/right) and treatment and will be kept by the randomiser in a sealed envelope until database lock. On day 1 the subjects in each dose group (n=8) will be randomised with regards to the treatment allocation of each wound. Two wounds per patient will receive TCP-25, and the other two will receive placebo. The proximal wound (R1 or L1) of one thigh and the distal wound of the other thigh (L2 or R2) will receive the same treatment, according to the assigned treatment allocation.

An unblinded research nurse in a nearby medical room will read the randomisation list, which indicates the assigned allocation of TCP-25 and control gel to the various wounds for each patient. The research nurse will then fill two syringes per patient. One syringe will contain TCP-25 gel and the other will contain placebo gel. Both syringes will be labelled with the randomisation number of the patient. Additionally they will be labelled with either ‘R1+L2’ or ‘R2+L1’, corresponding to the two wounds (right proximal+left distal or right distal+left proximal) that are to receive the contents of that syringe according to the assigned treatment allocation. These prefilled and labelled syringes will be provided to the blinded research staff who will then deposit their contents onto the correct combination of wounds indicated on the syringe label. In this way, the allocation will be communicated to the research staff while ensuring that they remain blinded to the treatment given to each wound.

If needed for emergency unblinding, sealed individual treatment code envelopes will be kept at the clinic and at a contract research organisation (Clinical Trial Consultants AB’s Pharmacovigilance department) in locked and restricted areas.

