**Methods and analysis:**

A randomised, double-blinded, first-in-human study was designed to evaluate the safety, tolerability and potential systemic exposure of three increasing doses of the TCP-25 gel applied topically on suction blister wounds in healthy adults. The dose-escalation will be divided into three sequential dose groups with eight subjects in each group (24 patients in total). Within each dose group, the subjects will receive four wounds, with two wounds on each thigh. Each subject will receive TCP-25 on one wound per thigh and placebo on one wound per thigh in a randomised double-blinded manner, with a reverse reciprocal position on each respective thigh, to a total of five doses over 8 days. An internal safety review committee will monitor emerging safety and plasma concentration data over the course of the study and must give a favourable recommendation prior to initiating the next dose group, which will receive placebo gel or a higher concentration of TCP-25 in exactly the same manner described above.

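### The Allocation section defines the wound codes with two opposite keys, so the gel given to each wound is certain only if one key was used at every step

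*Protocol article*

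**What the plan says.** All the relevant text is in the Allocation section of the protocol article.

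- The definition: "Wounds will be labelled R1 (right thigh, distal), R2 (right thigh, proximal), L1 (left thigh, distal) and L2 (left thigh, proximal". Here 1 means distal and 2 means proximal.
- The allocation rule, in the next paragraph: "The proximal wound (R1 or L1) of one thigh and the distal wound of the other thigh (L2 or R2" receive the same gel. Here 1 means proximal and 2 means distal.
- The syringe labels, which read R1+L2 or R2+L1, are explained as "corresponding to the two wounds (right proximal+left distal or right distal+left proximal". Read in order, R1 is right proximal and L2 is left distal, so this repeats the second key.

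The same section describes how the allocation reaches the wound. "The randomisation list will contain subject number, wound position, thigh (left/right) and treatment". An unblinded nurse in another room reads that list and fills and labels two syringes per subject. Blinded staff then "deposit their contents onto the correct combination of wounds indicated on the syringe label". The split within a subject is fixed: "Two wounds per patient will receive TCP-25, and the other two will receive placebo".

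**The concern.** This is the operative text that links the randomisation list, the syringe label and the wound, and it gives opposite anatomical meanings to all four codes. The list holds wound position and thigh as fields, while the syringe holds a code. Someone may therefore have to turn a position into a code, and someone else a code back into a position. If those two people use different keys, the gel goes to the wrong wounds.

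Local tolerability is a primary outcome, assessed wound by wound, and reactions judged worse than expected are also reported as adverse events (Data collection, Local tolerability). Every subject receives both gels, so the comparison of wounds within a subject is where placebo acts as a control. A mismatch would credit reactions to TCP-25 to placebo and the reverse. The safeguards described would not obviously reveal it: the gels look identical, each subject still has two active and two placebo wounds, and source data verification compares records that may carry the same ambiguous code. The safety review committee may break the code when deciding on further groups (Blinding), and the stored photographs, swabs and dressings would inherit any wrong label.

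**Working it through.** The plan gives no figure to reproduce here. The check sets the two keys side by side and follows each allocation through the chain.

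**Inputs** (Allocation section; group sizes from the Abstract, "three sequential dose groups with eight subjects in each group (24 patients in total"). Key A is the definition; key B is the allocation rule and the syringe-label sentence.

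| Code | Key A | Key B |
|---|---|---|
| R1 | right distal | right proximal |
| R2 | right proximal | right distal |
| L1 | left distal | left proximal |
| L2 | left proximal | left distal |

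**Step 1: the syringe labels.** R1+L2 is right distal with left proximal under key A, and right proximal with left distal under key B. R2+L1 is the reverse. Under either key a label names a diagonal pair, so the reciprocal design does not depend on the key. The two readings of one label share no wound.

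**Step 2: wounds given the wrong gel.** For each allocation (TCP-25 on R1+L2, or on R2+L1), count the wounds whose gel differs from the one intended.

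| List or syringe-filling key | Bedside key | Wounds wrong, either allocation |
|---|---|---|
| A | A | 0 of 4 |
| B | B | 0 of 4 |
| A | B | 4 of 4 |
| B | A | 4 of 4 |
| A | A on one thigh, B on the other | 2 of 4 |

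In the last row both TCP-25 wounds lie at the same level, both proximal or both distal, so the reciprocal position is lost as well. In every row the subject still has two active and two placebo wounds.

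**Step 3: the number of wounds that rest on the key.** 8 subjects × 4 wounds = 32 per dose group, and 24 × 4 = 96 in the planned trial. This is an upper bound on exposure to the ambiguity, not an estimate of error.

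**Step 4: illustration only.** Let d be the true TCP-25 minus placebo difference in the rate of local reactions, and m the share of subjects with a complete swap. The labelled difference has expectation (1 − m)·d + m·(−d) = (1 − 2m)·d.

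| Subjects swapped in a group of 8 | m | Factor 1 − 2m |
|---|---|---|
| 1 | 0.125 | 0.75 |
| 2 | 0.25 | 0.50 |
| 4 | 0.50 | 0 |
| 8 | 1 | −1 |

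The article supports no value of m. The formula covers complete swaps only. It does not cover a change of key between the five doses, which would expose the same wound to both gels.

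**The case against.** The strongest reply is that the contradiction may never have touched a wound. The article says that the wounds themselves are labelled with the codes, and the section on suction blister wound formation has the sites marked on the skin. If the codes were marked at the bedside, staff matched code to code and anatomy played no part. The position and thigh fields in the list may simply be 1 or 2 and R or L, which is the code itself. The article also condenses a full protocol, and the two later statements agree with each other, so one wrong list of labels introduced in condensing could explain everything.

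This stands as far as consequence goes: a swap needs two steps that use opposite keys, and the article shows no such step. It does not remove the contradiction. The article does not say that the codes are written on the skin, and the list, the labels and the eCRF are not shown.

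A reader might also infer more than the text supports:

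- That any error must be complete. It need not be: one mis-keyed thigh gives 2 of 4 wrong, and a change of key between doses gives mixed exposure.
- That local tolerability is the only outcome with a placebo control. Aggravated local reactions are also reported as adverse events, so wound-site adverse events share that control.
- That the factors above measure a bias. They are arithmetic on assumed shares, and the article's statistical analysis section describes summaries by treatment, not an estimated difference.
- That photographs would settle the matter. They could show at most the bedside positions, not which key the list or the unblinded nurse used.

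**Conclusion.** The Allocation section is wrong as written: two opposite keys are stated for all four codes and nothing in the article chooses between them. That part is certain. The consequence is conditional. With one key throughout, or codes matched to codes, 0 of 4 wounds are affected and only the anatomical description is at fault. With opposite keys at the list or syringe-filling step and at the bedside, 4 of 4 wounds in that subject receive the opposite gel, or 2 of 4 if one thigh is mis-keyed. The harm would then fall on local tolerability, wound-site adverse events and the exploratory wound material. Total dose per subject, plasma concentrations, ECG, vital signs, laboratory results and systemic adverse events would be unaffected.

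It would be tempting to read this as evidence that TCP-25 and placebo were exchanged. The article does not show that, nor which key was used in practice. The point must still be resolved before unblinding for analysis, because a mismatch could not be recognised from the blinded data and could weaken or reverse a primary comparison.

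**What to change.** Reconcile the three statements in the Allocation section to one key, and use that key in the protocol, randomisation list, syringe labels, eCRF, and photograph and sample labels.

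Before the code is broken for analysis, someone independent of the blinded team should confirm, for every dosed subject, that the same key was used at every step. The sources are the specification of the list, the syringe-label and preparation records, the bedside marking and the eCRF. Any mismatch should be documented, with the dose and thigh concerned, so that wounds are analysed by the gel they actually received.

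The cost is a text correction and a short reconciliation of existing records for the 24 planned subjects, plus any added under the extension that the Trial design and setting section allows. On the article's own dates there is room for it: publication was in February 2023 and analysis was to begin in April 2023.

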### Blinding

This is a double-blind study and the allocation of treatments will not be disclosed until a clean file has been declared and the database has been locked. The TCP-25 and placebo gels are identical in appearance.

**Unblinding** will only happen in the following situations:

The treatment code may only be broken by the Principal Investigator or delegate in case of emergency when knowledge of the treatment received is necessary for the proper medical management of the subject.The randomisation code may be broken by the iSRC during the assessment process (partial unblinding) to enable their decision on continued dosing of further cohorts. The medical staff and subjects will remain blinded to the treatment allocation.

### Data management

The data management routines include procedures for handling of the eCRF, database set-up and management, data entry and verification, data validation, quality control of the database and documentation of the performed activities including information of discrepancies in the process. Data validation/data cleaning procedures are designed to assure validity and accuracy of clinical data and consist of computerised online edit checks such as range checks and batch checks on data exports. All study-specific and standard data validation programming will be tested in a separate testing environment prior to use on production data. Detailed information on data management is described in a study-specific Data Management Plan.

Clinical data will be entered into an eCRF provided by Viedoc Technologies AB. Clinical data will be entered directly from the source documents or at bedside by authorised site personnel designated by the Investigator. All entries of data, corrections and alterations in the eCRF are to be made by the Investigator or designee, who is to be a qualified physician trained in Good Clinical Practice.

Because data entry is single, all data will undergo source data verification by monitors according to a risk-based monitoring plan. Monitors will review the eCRFs for completeness and consistency and compare data with the respective source documents. If corrections are needed, queries will be raised within the eCRF, either as a result of built-in edit checks or manually and corrected by the site staff. When all data have been entered and discrepancies solved, a clean file will be declared, the database will be locked and the code will be broken. The data analysis will begin in April 2023.

### Statistical analysis plan

Continuous data will be presented in terms of evaluable and missing observations, arithmetic mean, SD, median, minimum and maximum value. Categorical data will be presented as counts and percentages. When applicable, summary data will be presented by treatment, and by assessment time. Individual subject data will be listed by subject number, treatment and, where applicable, by assessment time. All descriptive summaries and statistical analyses will be performed using SAS V.9.4 or later (SAS Institute). Baseline will be defined as the last non-missing observation prior to the first administration of the intervention.

Outliers will be included in summary tables and listings and will not be handled separately in any analyses. Generally, no imputation of missing data will be performed. However, clinical safety laboratory parameters that are outside the detection limit, will be replaced with the detection limit when calculating statistics. Also, when calculating statistics for pharmacokinetics plasma concentrations, concentrations under lower limit of quantification will be replaced with lower limit of quantification if more than 50% of the values for a given time point is above lower limit of quantification. Otherwise, no statistics will be calculated for that time point.

### Data monitoring

#### iSRC

Before initiating a new dose group, all subjects in the previous dose group must have been treated and safety, tolerability and pharmacokinetics data (at least data up to 5 days for pharmacokinetics and 8 days for safety) for all treated subjects must have been evaluated by the iSRC. In case of non-replaced dropouts, available data for the dropouts will be included in the iSRC evaluation.

If TCP-25 is considered safe and tolerable, a written recommendation on the next dose level will be provided to the Sponsor.

The voting members of the iSRC will consist of the principal investigator or delegate and the chief physician at the Clinical Trial Unit or delegate. In addition, the study clinical research manager, the study pharmacokineticist and additional Sponsor representatives may be invited as appropriate. Further internal or external experts may be invited and consulted by the iSRC as appropriate.

The recommendation to the Sponsor may be study progression, to continue with a higher or lower dose than the intended dose, to repeat the same dose level, to continue with an intermediate dose level or to stop dosing. The recommendation of the iSRC on the next dose level will be made in consensus between the iSRC members and documented as appropriate.

In case there is disagreement between the two voting members, the most conservative approach will be taken.

#### Auditing

The Sponsor has employed a contract research organisation (Clinical Trial Consultants AB) as an independent monitor. Monitoring will be done according to a risk-based monitoring plan and the responsible monitor will periodically visit the study site at times agreed on by the investigator and the monitor. At each monitoring visit, the role of the Monitor includes, but is not limited to:

Confirm that facilities and resources remain acceptable.Confirm that the investigational team is adhering to the study protocol, applicable standard operating procedures, guidelines, manuals and regulatory requirements.Verify that data are being recorded in the eCRFs in an accurate and timely manner and that accountability checks are being performed.Verify that data in the eCRF are consistent with the clinical records in accordance with the monitoring plan.Verify that the correct informed consent procedure has been adhered to for participating subjects.Verify that AEs are recorded and reported in a timely manner and according to the clinical study protocol.Raise and escalate any serious quality issues, serious Good Clinical Practice breach and any data privacy breach to the Sponsor.

Centralised monitoring will also be performed continuously by study team members at Clinical Trial Consultants AB in accordance with the monitoring plan. When the study has been completed and all queries have been resolved and the database has been locked, the Monitor will perform a close-out visit.

Authorised representatives of the Sponsor, a competent authority or an independent ethics committee may also perform audits or inspections at the research clinic, including source data verification.

## Ethics and dissemination

### Ethical conduct of the study

The study will be performed in accordance with ethical principles that have their origin in the Declaration of Helsinki and are consistent with ICH/GCPE6 (R2), European Union (EU) Clinical Trials Directive and applicable local regulatory requirements. The principal investigator is responsible for submitting the study protocol, the subject information and informed consent form, any other written information to be provided to the subjects and any advertisements used for subject recruitment to the Swedish Ethical Review Authority for approval. The study has been approved by the Swedish Ethical Review Authority (registration number 2022-00527-01).

Before performing any study-related procedures the informed consent form shall be signed and personally dated by the subject and by the investigator. The subjects will be covered under the Sponsors liability insurance policy. The participating subjects are also protected in accordance with national regulations, as applicable.

### Subject data protection

The informed consent form includes information, that data will be recorded, collected and processed and may be transferred to other European Economic Area (EEA) or non-EEA countries. In accordance with the General Data Protection Regulation (EU) 2016/679, the data will not identify any persons taking part in the study.

### Clinical study report

A summarising report shall be submitted to the Swedish competent authority and independent ethics committee within 12 months after completion of the study. A clinical study report, in compliance with ICH-E3, describing the conduct of the study, any statistical analyses performed and the results obtained, will be prepared. The report will be reviewed and approved by, as a minimum, the principal investigator, the statistician and the Sponsor. The study results will be reported in the EudraCT database per applicable regulations within 12 months after completion of the study. All data obtained from any exploratory analyses will be reported separately.

### Publication and dissemination

Publication of the study results and access to the study data is at the discretion of the Sponsor. Authorship for any publications will be according to the Vancouver criteria. Subjects will be asked to provide a release for use of their photographs in publications if applicable. The subject has a right to refuse the photo release without jeopardising their eligibility to participate in the study.

### Patient and public involvement

Patients or the public were neither involved in the design nor will they be involved in this clinical trial’s conduct, reporting or dissemination plans.

### Protocol version

Protocol V.2.0; 25 January 2022. Protocol amendments will be promptly communicated to all relevant parties, trial registries and to the ethics committee and competent authority as required by law.
